## Abstract

**Background:**

Blood pressure is a primary cardiovascular disease risk factor. Population-wide governmental strategies aim to reduce lifestyle and dietary risk factors for hypertension, one of which is an unbalanced diet with high sodium and low potassium intakes. Nutrition interventions in the workplace are considered a promising approach in encouraging health-promoting behaviors. We developed and conducted the health promoting sodium reduction trial “Healthful & Tasty: Sure!” in worksites in the German-speaking part of Switzerland from May 2015 to Nov 2016, for which we present the study protocol and baseline characteristics.

**Methods:**

Healthful & Tasty, a cluster nonrandomized single-arm trial with calibration arm, aimed to demonstrate the effectiveness of a combined educational and environmental intervention in the workplace in reducing employees’ average daily sodium/salt intake by 15%. To this end, health and food literacy of employees and guideline compliance among the catering facility team needed to be improved. The primary outcome measure was sodium/salt intake estimated from sodium excretion in a 24-h urine sample. Secondary outcome measures included changes in the overall qualitative diet composition, blood pressure, anthropometric indices, and health and food literacy.

Of eight organizations with catering facilities, seven organizations took part in the nutrition education and catering salt reduction interventions, and one organization participated as a control. Overall, 145 consenting employees were included in the staggered, one-year four-phase trial, of which 132 participated in the intervention group. In addition to catering surveys and food sampling, the trial included five follow-up health assessments including questionnaires, blood pressure measurements, anthropometrics, and sodium, potassium, and iodine intake measurements obtained from 24-h and spot urine samples, and a food record checklist. Exploratory and hypothesis generating baseline statistical analysis included 141 participants with adequate 24-h urine samples.

**Discussion:**

Despite practice-driven limitations to the study design and small cluster and participant numbers, this trial has methodological strength and will provide important insights into the effectiveness of a combined educational and environmental intervention to reduce salt intake among female and male Swiss employees.

**Trial registration:**

German Clinical Trials Register, DRKS00006790. Registered 23 September 2014.

## Background

Stroke and ischaemic heart disease are the most common noncommunicable diseases and causes of disability and death worldwide [1, 2]. These cardiovascular diseases (CVD) impose a large economic burden: in Switzerland the annual direct health care costs attributable to CVD were estimated to be CHF 10.3 billion in 2011 [3].

About half of CVD events are estimated to be attributable to high blood pressure [4]. Yet many people are unaware of being hypertensive [5, 6], and strokes and ischaemic events often occur without prior diagnosis of hypertension [7]. Population-wide governmental strategies aim to lower dietary and other lifestyle risk factors for hypertension/CVD and promote protective factors [8, 9]. Experts acknowledge the health protective, blood pressure reducing role of a restricted sodium (Na) intake below an average of 2 g (87 mmol) per day [10, 11]. In addition, a sufficient potassium (K) intake (> 3.5 g (90 mmol)/day) and a dietary Na/K ratio below 0.6 by weight (< 1 by mmol) is a related public health goal [12]. Countries worldwide have established national programs for stepwise shifting of the overall population Na intake distribution [13] towards 30% lower intakes [14, 15].

Based on research on population Na intake [16, 17] and Na content of foods/catering offerings [18–20], the Swiss salt strategy defined an intermediate goal for Na intake reduction of at least 16% for the population in four years. That is, from an average of 3.5 g to below 3 g Na, or from 9 g to less than 8 g salt equivalent (short salt, NaCl) intake per day [21] -the final long-term target being 5 g/day [10]. The food industry, excepting food service (catering), became involved in a voluntary reformulation program [22] to reach defined Na goals (e.g., [23]). However, actions targeting eating behavior to reduce Na intake have not been pursued in the absence of consistent evidence of their effectiveness [24]. The national research program NRP69 Healthy Nutrition and Sustainable Food Production, which was seeking practical answers to how people in Switzerland can achieve a healthy diet, offered a framework to investigate feasible ways of Na intake reduction [25].

About three-quarters of the adult Swiss population eats lunch away from home [26], and almost 15% of the general population is estimated to frequent communal catering [27]. Persons regularly eating in staff canteens tend to follow a Western, unhealthy, diet [28], and structural catering initiatives were rated helpful in promoting healthy food choice [29]. The World Health Organization (WHO)/World Economic Forum [30] and the FAO Nutrition Division [31] encourage nutrition interventions in the workplace setting because women and men in the age range of 15 to 65 years can be reached repeatedly, and health-promoting behavior may thus be sustainably influenced. Moreover, Shain & Kramer [32] emphasized that only health promotion interventions in the workplace that address individual as well as environmental influences will be effective, and Eickolt et al. [33] argued that an environment -such as an organization with a staff canteen- conducive to learning supports enhancement of health literacy.

We thus developed a combined educational and environmental intervention in the workplace that aimed at reducing employees’ Na intake by 15% in one year and supposed that with enhancing generic and nutrition-specific health literacy participants’ social networks may also benefit from transfer of knowledge and skills.

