### Study design

Healthful & Tasty is a combined educational and environmental trial in the Swiss workplace to promote health by lowering Na intake in a nutritionally balanced, healthy diet. Health promotion activities in the workplace are typically driven by legal responsibilities for occupational health and safety in Switzerland. Nutrition education and structural measures in catering facilities are not standard components in the national program Friendly Work Space [35]. Moreover, many organizations with staff canteens outsource catering and related food health responsibility to large catering firms, which offer labeled, nutritious menus. The trial recruited organizations and their employees, but catering firms had to agree to the intervention as well. We established a cluster randomized controlled trial (cRCT), received ethical approval by Swissethics, and registered the trial in September 2014.

Considering experiences from our own studies in communal catering [18, 19, 36, 37] and reports in the literature [38–41], and in agreement with the NRP69 scientific steering committee we prepared for having to adjust the study design if recruitment with randomization and matching at cluster level proved to be infeasible within six months (Table 1).

**Table 1 Tab1:** Study design options of the “Healthful & Tasty: Sure!” workplace trial

	Experimental study design	Alternative quasi-experimental study design
Design	Cluster randomized controlled trial	Cluster nonrandomized single arm trial with calibration arm
Blinding	No	No
Pair-wise matching	Yes	No
Sample size estimation (power calculation)	Assumptions: baseline mean 24-h urine sodium excretion of 180 mmol [16, 17, 42], standard deviation of 65, intra-cluster correlation coefficient of 0.05, 16 clusters and drop-out rate of 25%. Objective: detect between-group difference of at least 15% (i.e. 27 mmol) at trial end with alpha 0.05 and 80% power.	Assumptions: baseline mean 24-h urine sodium excretion of 180 mmol [16, 17, 42], standard deviation of 65, intra-cluster correlation coefficient of 0.05, and drop-out rate of 10%. Objective: detect sodium intake reduction by 15% (i.e. 27 mmol) until trial end with alpha 0.05 and 80% power.

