Numbers required to measure effectiveness	Number of clusters (participants, before 25% drop-out) 8 intervention clusters (*N* = 395, 50 per cluster) 8 control clusters (N = 395, 50 per cluster)	Number of clusters (participants, before 10% drop-out) 7 intervention clusters (*N* = 112, 16+ per cluster)

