### Statistical analysis

For baseline analysis, continuous variables were summarized descriptively using mean and 95% confidence interval (CI) or median and range depending on sample size and type of variable. For categorical variables, we used frequency and percentage. Variables were summarized overall, separately for intervention and control group, and by sex. At cluster level, Na, K, and NaCl levels of menu components were calculated weighted for sales numbers. At participant level, comparisons between groups were performed using t-tests for continuous variables, and chi-squared tests or Fisher’s exact tests for categorical variables depending on the expected number per cell. We applied two-tailed tests with significance level 0.05 for all analyses. Because baseline analysis was exploratory and hypothesis generating, no adjustment for multiple testing was done.

We used and will use baseline data to explore factors related to salt intake and evaluation of questionnaires. Statistical analyses are described in the respective articles [71, 91]. Future analysis will include application of a linear mixed model with organization as random effect to assess the change in primary outcome from t0 to t12. All analyses are run using R 3.3.2 [92].

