Our experience showed that implementing intervention trials in the workplace is highly sensitive to how the real-world setting meets scientific demands [100, 101]. We chose a cRCT, which is commonly viewed as the most reliable design to assess the effectiveness of interventions and avoid bias [102]. However, the enrollment rate of organizations in our trial was much lower than expected, and interested organizations did not accept being randomized to intervention or control arms, which confirms observations made by Kwak et al. [39] who recognized randomization as one of the most important reasons why organizations refuse to participate in trials. For these reasons, and time constraints, we adjusted to a quasi-experimental study design. The final, cluster nonrandomized single-arm trial with calibration arm still allows following all participants and estimating intervention effectiveness with sufficient robustness [41, 103]. Participation at individual level was modest, but we anticipated a high follow-up rate since most participants seemed committed to participating in education workshops during the workday, and receiving regular measurement results of blood pressure, weight, Na and K intake, etc., as well as coupons for eating in the staff restaurant as compensation at study end.

We will use the RE-AIM (reach, effectiveness, adoption, implementation, and maintenance) framework [104] to estimate the trial’s final overall impact. Finally, we recognize that study findings can only be applied to similar organizations, not to the overall working population in Switzerland, since only certain German-speaking cantons were included and sample size was small.

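### The primary outcome is a comparison with a control group, but the final design is sized on, and its named model describes, a within-arm change that a 13-person calibration arm cannot correct for background decline

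*Protocol article*

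**What the plan says.** All references are to the protocol article.

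- **Objective and outcome.** Study objectives, Primary outcome measure and Intervention design all set the intervention arm against a control: consumers of ordinary canteen meals, a control group, and organisations without intervention.
- **Sizing of the final design.** Table 1 (Study design), column for the quasi-experimental design, assumes "baseline mean 24-h urine sodium excretion of 180 mmol" and "standard deviation of 65, intra-cluster correlation coefficient of 0.05, and drop-out rate of 10" percent. The aim is to "detect sodium intake reduction by 15% (i.e. 27 mmol) until trial end with alpha 0.05 and 80% power". The result is "7 intervention clusters (*N* = 112, 16+ per cluster", labelled as before drop-out. No control arm and no allowance for background change enter this calculation.
- **Model.** Statistical analysis says that future analysis will include a "linear mixed model with organization as random effect to assess the change in primary outcome from t0 to t12". No group or trend term is named.
- **Size of the control.** Participation reports seven intervention organisations and one control organisation, with 132 and 13 employees.
- **Claim.** Strength and limitations says that the final design "still allows following all participants and estimating intervention effectiveness with sufficient robustness". It does not say how the calibration arm enters the estimate.
- **Background change.** The Background reports a national goal of "at least 16% for the population in four years", and says that the food industry, apart from catering, "became involved in a voluntary reformulation program".

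**The concern.** The quantity that the trial says it will estimate (a between-group difference in change) is not the quantity for which it was sized or which its named model describes (a change over time). The two agree only if sodium excretion would have stayed level without the programme, or if the control arm can measure how far it would not have.

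If neither holds, a fall that would have happened anyway is credited to the programme. That raises the chance of claiming an effect where there is none, and brings the 15% target closer than the programme alone would. The article itself describes a national effort that could lower sodium intake, so a rival explanation for a fall is on the page.

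**Working it through.** **Inputs.** Mean 180 mmol, SD 65, ICC 0.05, drop-out 10%, target 27 mmol, 7 clusters, N = 112 (all Table 1); control arm of 1 organisation and 13 people (Participation); 128 intervention participants with adequate baseline urine (Table 3); two-sided 0.05 (Statistical analysis). Table 1 does not say whether 65 is the SD of one measurement or of the change. I use two values for the SD of change: 65 (within-person correlation 0.5) and 65 × √2 = 91.9 (correlation 0). I also assume that the ICC of 0.05 applies to the change.

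**1. The stated sample size.** Within-arm formula, 16 per cluster:

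- n = (65 × (1.96 + 0.84) / 27)² = 45.5
- design effect 1 + 15 × 0.05 = 1.75
- 45.5 × 1.75 / 0.9 = 88.5, so 89

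With SD 91.9 the same steps give 177. With SD 65 and a t test on 6 df, 112 analysed gives 79.0% power, and 101 analysed (112 less 10%) gives 76.7%. So 112 is plausible for a within-arm change against zero, though the text does not fix one route to it.

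**2. What the calibration arm can measure.**

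- Design effect for 13 people in one organisation: 1 + 12 × 0.05 = 1.6
- SE of the control change, SD 65: √(65² × 1.6 / 13) = √520 = 22.8 mmol
- SE of the control change, SD 91.9: √1040 = 32.2 mmol

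A 95% interval for the control change is thus about ±45 to ±63 mmol, wider than the 27 mmol target in each direction. This borrows the ICC from Table 1; one organisation supplies no estimate of variation between control organisations.

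**3. The between-arm difference.** Intervention arm: 128 people, 128/7 = 18.3 per cluster, design effect 1 + 17.3 × 0.05 = 1.86.

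- SE of the intervention change: √(65² × 1.86 / 128) = 7.8 mmol (SD 65), 11.1 mmol (SD 91.9)
- SE of the difference: √(22.8² + 7.8²) = 24.1 mmol; √(32.2² + 11.1²) = 34.1 mmol
- Power for 27 mmol (normal): 27/24.1 = 1.12, about 20%; 27/34.1 = 0.79, about 12%

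**4. Illustration: background fall, no intervention effect.** The trend here is an assumption. The goal taken linearly is 16/4 = 4% per year, or 0.04 × 180 = 7.2 mmol (7.2/27 = 27% of the target). Half of that is 3.6 mmol (13%). The SE of the intervention change with 101 completers (14.4 per cluster, design effect 1.67) is √(65² × 1.67 / 100.8) = 8.37 mmol, or 11.83 mmol with SD 91.9.

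Probability of a significant reduction, t on 6 df to normal:

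| Assumed background fall | SD of change 65 | SD of change 91.9 |
|---|---|---|
| 0 | 2.5% | 2.5% |
| 2% per year (3.6 mmol) | 5.6 to 6.3% | 4.4 to 4.9% |
| 4% per year (7.2 mmol) | 11.0 to 13.6% | 7.5 to 8.8% |

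With 112 analysed, the largest of these rises only to 14.1%.

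**5. The goal in grams.** The Background restates the goal as 3.5 g to below 3 g sodium, or 9 g to below 8 g salt. Taken as absolute amounts over four years, these are 500/23/4 = 5.4 mmol and 1000/58.5/4 = 4.3 mmol per year, that is 3.0% and 2.4% of 180. As percentages of their own starting values they are 14.3/4 = 3.6% and 11.1/4 = 2.8% per year. All lie between the 2% and 4% rows.

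**The case against.** Three points deserve weight.

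**The plan does not say that the uncontrolled change is the effect.** A reader might infer from the sizing and the model sentence that any fall over the year will simply be counted as intervention effect. The documents do not support that: the objective, the primary outcome and the design description all name a control comparison, and both arms are followed every three months. The model sentence is a one-line summary that neither states nor excludes a group term, and the full plan may contain one. This stands, and I do not rely on the absence of such a term. The size of the control arm is the obstacle whether or not the term is there.

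**A concurrent decline is not shown.** A reader might also infer that sodium intake was falling by 4% per year during the trial. The Background gives a policy goal, does not date the four years, reports no achieved fall, and puts catering outside the reformulation programme. All of this stands. The catering exclusion does not remove the possibility, because the outcome is total 24-h excretion and covers all food eaten; in Table 3, 100 of 141 participants (71%) ate lunch in the canteen three times a week or less.

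**The largest error figure is an upper end.** About 14% needs the 16% goal met in full, an SD of change of 65 and a normal reference distribution. The gram figures imply smaller trends and the larger SD lowers the result. This stands, so the range has to be given with its lower end.

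The article does admit practice-driven limits to the design and small numbers. It does not mention background change among them.

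**Conclusion.** The point holds as an inconsistency with a consequence for the claim. The outcome is between-group, whereas the sizing and the described model are within-arm. The arm meant to bridge the two has an SE of about 23 to 32 mmol for its own change and leaves about 12 to 20% power for the 27 mmol difference. It can neither detect nor exclude a background fall of a few mmol. The statement of robust estimation is therefore not supported for attributing the change to the programme, although the 12-month change itself can be estimated.

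Bias from a background trend is possible and bounded, not demonstrated. Under an assumed fall of 2 to 4% per year and no intervention effect, the chance of a significant reduction is about 4 to 14%, against 2.5% nominally. With no trend it stays at 2.5%. These figures rest on an SD of change of 65 to 92 mmol, an ICC of 0.05 for the change, and 101 to 112 people analysed.

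**What to change.** 1. Report the t0 to t12 estimate in the intervention arm as the 12-month change. Beside it, show the between-arm difference that the primary outcome calls for, with its interval, and state that it is imprecise. Say in one sentence how the calibration arm enters the primary estimate.
2. Add a sensitivity analysis that tests the 12-month change against an assumed background decline of 0 to 4% per year (0 to 7.2 mmol), and give the decline at which the conclusion is lost. Label the range as an assumption.
3. Qualify the robustness sentence in Strength and limitations, name background change as a limitation, and claim a 15% intervention effect only if it survives step 2.

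The main analysis is described as still to come, so this is feasible. It needs no new data. The cost is a few lines of analysis and wording, and a more cautious claim.

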## Methods

We followed the CONSORT guidelines for reporting trials [34].

### Study setting

The worksite-based intervention trial Gesund & Gut: Na Klar! (Healthful & Tasty: Sure!) was conceived for implementation in the German-speaking part of Switzerland. It was restricted to eight of the 26 Swiss cantons for language, logistical, and economic reasons. The experimental population consisted of female and male employees, aged 15 to 65 years, with access to small (≤ 150 luncheons/day), medium (151–500 luncheons/day), and large (> 500 luncheons/day) staff canteens of both public and private organizations.

### Study design

Healthful & Tasty is a combined educational and environmental trial in the Swiss workplace to promote health by lowering Na intake in a nutritionally balanced, healthy diet. Health promotion activities in the workplace are typically driven by legal responsibilities for occupational health and safety in Switzerland. Nutrition education and structural measures in catering facilities are not standard components in the national program Friendly Work Space [35]. Moreover, many organizations with staff canteens outsource catering and related food health responsibility to large catering firms, which offer labeled, nutritious menus. The trial recruited organizations and their employees, but catering firms had to agree to the intervention as well. We established a cluster randomized controlled trial (cRCT), received ethical approval by Swissethics, and registered the trial in September 2014.

Considering experiences from our own studies in communal catering [18, 19, 36, 37] and reports in the literature [38–41], and in agreement with the NRP69 scientific steering committee we prepared for having to adjust the study design if recruitment with randomization and matching at cluster level proved to be infeasible within six months (Table 1).

**Table 1 Tab1:** Study design options of the “Healthful & Tasty: Sure!” workplace trial

	Experimental study design	Alternative quasi-experimental study design
Design	Cluster randomized controlled trial	Cluster nonrandomized single arm trial with calibration arm
Blinding	No	No
Pair-wise matching	Yes	No
Sample size estimation (power calculation)	Assumptions: baseline mean 24-h urine sodium excretion of 180 mmol [16, 17, 42], standard deviation of 65, intra-cluster correlation coefficient of 0.05, 16 clusters and drop-out rate of 25%. Objective: detect between-group difference of at least 15% (i.e. 27 mmol) at trial end with alpha 0.05 and 80% power.	Assumptions: baseline mean 24-h urine sodium excretion of 180 mmol [16, 17, 42], standard deviation of 65, intra-cluster correlation coefficient of 0.05, and drop-out rate of 10%. Objective: detect sodium intake reduction by 15% (i.e. 27 mmol) until trial end with alpha 0.05 and 80% power.
Numbers required to measure effectiveness	Number of clusters (participants, before 25% drop-out) 8 intervention clusters (*N* = 395, 50 per cluster) 8 control clusters (N = 395, 50 per cluster)	Number of clusters (participants, before 10% drop-out) 7 intervention clusters (*N* = 112, 16+ per cluster)

### Recruitment

Based on our power calculation for cRCT sample size, we estimated the need for eight intervention and eight control clusters, each with 50 participants per cluster to detect a between-group difference of at least 15% in mean 24-h Na excretion in urine at trial end with alpha 0.05 and 80% power [16, 17, 42] (Table 1). The two-stage cluster sampling started in November 2014. Following an intermediate recruitment evaluation in April 2015, we switched design as shown in Table 1. By then 60% of 389 potential clusters had been resolved, and seven organizations and their catering facilities had agreed to participate but did not accept random allocation to the intervention or control arm. The design change had no impact on sampling procedures and documents at the individual participant level, the ethics committee approved the change, and the clinical trial registration was updated and annotated. Recruitment at cluster level was stopped due to time constraints at the end of October, 2015, in virtue of having achieved the estimated minimum sample size (seven intervention clusters, at least 112 participants).

